### 2.2 Participants

Participants were recruited via secondary schools in Flanders, Belgium. Years 1 to 4 (1st and 2nd grade) of general secondary education were invited to participate, referring to ages 12 – 16. Five different schools (spread across three provinces) participated in the study. Each school selected one pair of parallel classes, which resulted in five pairs of classes (two of the first year, one of the second year, and two of the third year). In total, 188 adolescents participated in the study. Of all the adolescents, 95 were in the PET program (*M*_age_ = 13.2, SD_age_ = 1.00) and 93 in the CREAT program (*M*_age_ = 13.3, SD_age_ = 1.08). Gender distribution was approximately the same in both groups (PET program: 73.6% females, 25.3% males, 2.1% other; CREAT program: 76.3% females, 22.6% males, 1.1% other).

### 2.3 Procedure

The procedure of the RASPERA-study is shown in the SPIRIT schedule of enrolment, interventions, and assessments (Supplementary Figure 1). Several secondary schools were invited for study participation via email. Schools that expressed an interest in the study received more detailed information, in-person at school or via an online meeting. Following the selection of parallel classes by the schools, one of the involved researchers gave a short oral presentation at the schools to inform the adolescents about the background of the study, procedure, potential risks and benefits, the voluntary character of participation and information about the informed consent procedure. In this way, adolescents were informed about all study phases and potential consequences, and they had the opportunity to directly ask for clarification if needed. In case any questions arise afterwards, contact information of the researchers was shared.

Immediately following the oral presentation, each adolescent received two printed booklets with a summary of the study and the informed consent form in duplicate (i.e., exemplar researcher and adolescent/parent). One booklet was addressed to the adolescent and the other to their parent(s). Adolescents and their parents were invited to sign their versions of the informed consent in duplicate. In consultation with the school, a deadline was agreed on for the adolescents to hand in the two signed versions of the informed consent. Direct access to the school communication platform was asked for as contact information of participants and their parents is integrated in this platform, which was needed to provide participants with their unique participation code.

Subsequently, participants completed the baseline assessment online, which consisted of a series of self-report questionnaires. It is only after completion of this first assessment that the researcher who was coordinating the study in the schools and who delivered the trainings was informed about the result of the random allocation (conducted by an independent statistician) of classes to one of the two conditions. The training programs started 1 week after the first assessment, and, in every school, classes received training sessions on the same days. Furthermore, training sessions were delivered by a researcher without a teacher being present. In that way, contextual variation across sessions and classes was kept to a minimum (e.g., no confounding effects related to the presence of a particular teacher). In addition, efforts were made to ensure that both trainings closely resembled in terms of format, structure, intensity, interaction between adolescents, invitations to practice with the skills taught during the in-class sessions. In this way, we aimed to prevent that adolescents would start to speculate about study hypotheses.

After completion of the trainings, adolescents of both groups took part in two final assessments. That is, a similar series of self-report questionnaires were presented 1 week (post-training) and, again, 2 months after the final training session (follow-up). Assessments in parallel classes (i.e., same school) were administered at the same day to minimize potential confounding effects by contextual factors. Per assessment, completing the self-report questionnaires took approximately 60–90 min. Self-report questionnaires were administered via Qualtrics (GDPR-proof online survey platform) on the laptop/tablet of the participants at school, with the intention to minimize errors due to manually entering data and missing values (i.e., “request response” option if questions were not completed). One of the involved researchers was present during the assessments, so participants could ask questions if necessary.

At the end of the study, participants will receive a €25-voucher for Bol.com (a local online store) as an incentive. In addition, participants and participating schools will be debriefed via email about our specific hypotheses and they will have the possibility to contact the researchers for additional information. Participating schools will automatically be informed about the general results.

### 2.4 Training programs

#### 2.4.1 Positive Events Training (PET)

The PET program is a group-based training program combining Memory Specificity Training [MEST; (39)] and Future Event Specificity Training [FEST; (14)]. It comprises four sessions of 50 min that are delivered for four consecutive weeks. The training is delivered in a standardized manner, using the PET program manual developed for this study, with content adapted from our MEST and FEST manuals. Following brief psychoeducation on the rationale behind the PET program (i.e., recalling and anticipating specific positive events has been found to be beneficial for mental wellbeing), participants practice in generating detailed specific memories (Sessions 1 and 2) and future events (Sessions 3 and 4) using neutral and positive cue-words. Homework, including exercises that resemble those used in the training sessions, is provided after every session to stimulate adolescents to further practice at home. During the sessions the trainer explained the homework exercises to the adolescents and encouraged the adolescents to actively engage with the homework material by emphasizing its importance. At the start of each session, the trainer checked if everyone completed their homework which meant that adolescents also were aware that completion of homework was being monitored. Moreover, adolescents received additional practice material after the final training session to continue practicing their skills.

#### 2.4.2 CREAtive writing Training (CREAT)

The control training or CREAtive writing training (CREAT) follows the exact same format and length as the PET program (i.e., delivered by a trainer in group over 4 × 50-min sessions, delivered for four consecutive weeks, including homework exercises after each session and additional material at the end of the training). Following brief psychoeducation on the rationale behind the PET program, participants completed a series of creative writing exercises – which are not self-referential – using funny and thought-provoking writing prompts. They were explicitly instructed not to write about themselves as the main character in their stories, to mitigate against the risk of partially triggering expected working mechanisms of the PET program. Concerning the rationale, participants were told that creative writing has been found to be beneficial for mental wellbeing, as they cultivate creativity and stimulate imagination skills. A similar CREAT program has been successfully used before in an online version as a control training for a memory specificity training (12).

### 2.5 Outcomes

Primary outcomes are resilience and mental wellbeing. Secondary outcomes are positive affect, positive affect regulation and anhedonia.

#### 2.5.1 Self-report questionnaires

In the self-report questionnaires below adolescents were instructed to consider and rate their experiences of the past 2 weeks. All scales have proven psychometric quality (see below) and have been used successfully in adolescents before (6, 40–43). Means of the scales will be calculated as final scores of the questionnaires.

The short version of the Connor-Davidson Resilience Scale [CD-RISC (44–46) translated into Dutch by Danhof-Pont and Schrier (47)] was used to assess resilience (primary outcome). This scale consists of 10 items (e.g., “Dealing with stress makes me stronger”) that are rated on a 5-point scale going from 1 (*not at all*) to 5 (*very often*), with higher scores indicating higher resilience (total score: minimum = 10, maximum = 50). The CD-RISC shows good construct validity, convergent and divergent validity, test-retest reliability, and good internal consistency with a Cronbach's alpha value of 0.85 in young adults (44, 45).

Mental wellbeing (primary outcome) was measured using the Short Warwick-Edinburgh Mental Wellbeing Scale (SWEMWBS) (48, 49). The SWEMWBS consists of seven statements (e.g., “I was optimistic about the future.” or “I felt useful.”) that are scored on a 5-point scale ranging from 1 (*never*) to 5 (*always*). Higher scores reflect higher mental wellbeing (total score: minimum = 7, maximum = 35). There is evidence for good convergent, construct and discriminant validity and for high internal consistency (α = 0.88) in an adolescent sample (48, 50, 51).

The Positive Affect subscale of the Positive and Negative Affect Schedule Scales (PANAS) was administered to assess positive affect (secondary outcome) (52, 53). The Positive Affect subscale of the PANAS consists of 10 items (words) that describe positive feelings (e.g., “excited”). Items are rated on a 5-point scale going from 1 (*very slightly or not at all*) to 5 (*extremely*), with higher scores reflecting higher positive affect (total score: minimum = 10, maximum = 50). The scale has good convergent and discriminant validity and good internal consistency (Cronbach's alpha of 0.79) in a sample of adolescents (52–54).

The Responses to Positive Affect scale, child version (RPA-C) (55–57) was used to assess positive affect regulation (secondary outcome). The RPA-C consists of items reflecting both dampening (e.g., “When you felt happy, how often did you think: ‘I don't deserve this'?”) and savoring responses (e.g., “When you felt happy, how often did you notice that you felt full of energy?”). All 17 items are rated on a 4-point scale ranging from 1 (*not at all*) to 4 (*very often*). The minimum total score a participant can get on the RPA-C is 17, the maximum is 68. There is evidence for good convergent and incremental validity and internal consistency for each scale is sufficient to good (Cronbach's alpha ranges from 0.72 to 0.86) in both children and (young) adults (55–57).

Symptoms of anhedonia (secondary outcome) were measured using the Leuven Anhedonia Self-report Scale (LASS, 2nd version) (58). All 12 items (e.g., “There were few things I looked forward to.”) are rated on a 5-point scale going from 1 (*completely untrue*) to 5 (*completely true*) with higher scores reflecting higher levels of anhedonia (total score: minimum = 12, maximum = 60). The total scale of the LASS has good internal consistency with a Cronbach's alpha value of 0.81 (58) and there is evidence for good convergent and discriminant validity in a sample of adolescents (31).

The Depression Anxiety Stress Scale (DASS-21) (59) was used to assess basic mental health to control for baseline differences in the training groups, and to explore the generalized effect of the PET program on levels of depressive symptoms and stress at post-training and at follow-up. The DASS-21 consists of 21 items (e.g., “I felt like my life had no meaning.”) that are rated on a 4-point scale going from 0 (*never*) to 3 (*almost always*), with 0 as a minimum total score, and 63 as a maximum total score. There is evidence for good construct and concurrent validity and good internal consistency of the subscales of the DASS-21 in both adolescent and adult samples, with Cronbach's alpha ranging from 0.79 to 0.94 (60, 61).

#### 2.5.2 Manipulation checks

The Episodic Future Thinking Test (EFT-T) (14, 62) was used to assess episodic future thinking specificity. For each assessment point, a different set of eight cue positive or neutrally-valenced words (e.g., love, street) were presented. The cue-word sets were composed of cue words balanced in their valence, arousal and frequency of occurrence based on Moors et al.'s (63) norms for Dutch words. Alternately, participants were asked to generate a positive future event that is related to a positive or neutral cue word (i.e., positive – neutral – positive – neutral cue word etc.). For this study, the original EFT-test was slightly adapted as participants were asked to generate *only* potential positive future events regardless of the cue word valence.

The Autobiographical Memory Test (AMT) (39) measured positive memory specificity. Similar to the EFT-T, the AMT was slightly adapted compared to the original version: participants were asked to write down one specific positive memory the cue-word reminds them of regardless of the cue-word valence (parallel to the EFT, four positive and four neutral in an alternating order). For the AMT, the same sets of cue words as in the EFT-test were presented to participants. However, cue words used in the EFT-test and AMT of the same assessment point were different. Also, the cue-word set used in the AMT at T1 was not used for the EFT-test at T2, as retrieval of positive memories at T1 might have influenced the process of generation of positive future events at T2 (e.g., rewording memories into positive future events instead of simulating new expected positive events).

#### 2.5.3 Non-validated questionnaires

The AMT and EFT-test were complemented by a series of single-item ratings (14, 39) following each cue-word. First, two single-item ratings of the anticipated/anticipatory (future) or remembered/felt pleasure (past) associated with the events participants recall/generate on the AMT and EFT-T were administered. Second, participants were asked to complete two single-item ratings of the level of detail and mental imagery associated with the events they recall/generate on the AMT and EFT-T. As part of the EFT-test only, two additional single-item ratings of perceived control and perceived likelihood of occurrence associated with the generated future events were assessed. Finally, two additional single-item ratings of anticipated/anticipatory (future) or remembered/felt positive feelings (i.e., not solely pleasure) (past) associated with the events participants recall/generate on the AMT and EFT-T were administered. Mean scores of these single-item ratings will be calculated.

The Leuven Exeter Dampening Scale-General (LEDS-G; Bogaert et al., unpublished) is a newly developed self-report scale, aimed at covering a larger variety of dampening appraisal styles compared to traditionally used scales. The LEDS-G consists of 13 items (e.g., “I can only be happy if others are too.”) that are rated on a 5-point scale going from 1 (*almost never*) to 5 (*almost always*), with 13 as a minimum total score, and 65 as a maximum total score.

A Dutch (non-validated) version of the 10-item-version of Abridged Ways of Savoring Checklist for Adolescents (savoring scales) (64) was used to assess savoring. Items (e.g., “I looked for other people to share it with.”) are rated on a 7-point scale going from 1 (*totally disagree*) to 7 (*totally agree*), with higher scores reflecting higher levels of savoring (total score: minimum = 10, maximum = 70).

As part of the second assessment point, adolescents were asked about the extent to which they actively engaged in the training and actually completed the homework exercises. Additionally, some questions about their personal experiences with the training were presented. As part of the final assessment, adolescents were asked to which extent and how they continued practicing the skills they learned during the training. Finally, they were asked a few questions about the perceived impact of the training.

### 2.6 Harms

The EFT-test and AMT are not expected to have possible disadvantages for participants, as they do not directly assess (expressions of) mental health or wellbeing. Instead, they explicitly focus on positive generated future thoughts and memories. Some of the self-report questionnaires do tap into aspects of mental health (e.g., resilience, mental wellbeing, anhedonia) though, which may result in some adolescents becoming aware of their engagement in suboptimal ways of regulating positive emotions, low levels of positive emotions, etc. However, such gained insights in one's own mental wellbeing and ways of regulating emotions should not necessarily be considered problematic. It may rather encourage participants to pay (more) attention to their mental wellbeing and ways to enhance it.

Irrespective of the experienced impact – if any – of the baseline assessment, the intervention group was offered the PET program immediately afterwards. The PET program aims to stimulate resilience and mental wellbeing, increase levels of positive emotions, and create a shift toward more adaptive ways of positive emotion regulation. In addition to participants of the intervention group, participants of the control group may benefit from their active control training (CREAT). We do not rule out the possibility that participants in the CREAT program would also experience (some) positive effects from that training by focusing on positive emotions (since they are asked to write down funny and non-realistic stories) and non-training-related factors of the training. Furthermore, as part of the informed consent, participants were provided with a list of relevant contact points if they experience the need for counseling (including specific services for youngsters such as www.awel.be, [name]; www.tele-onthaal.be; jongerenadviescentra). This information was referred to again at the three assessment phases.

### 2.7 Data management

Age and demographic data (month of birth, year of birth, gender, ethnicity, school, class, grade) were recorded. Participants were asked to fill in a unique participant code (received via the school communication platform before the actual assessment), so their name cannot be directly linked to the data collected in this study (i.e., in the same Qualtrics survey). As soon as data collection is finished (including linking of data of the three assessment points), the file in which names of participants are linked with the unique codes, will be deleted.

The school communication platform was used to send participants their unique codes and practical information about the study. As part of both trainings, participants were handed over a printed version of the exercise sheets (during sessions) and worksheets (homework). If needed, a digital version of the worksheets was sent via email. All contact information will be deleted as soon as data collection is finished. As part of the informed consent, participants could fill in their email address if they want to be informed about the general study findings. After communication of the findings, this list with contact information will be deleted.

Qualtrics, the platform that was used for the assessments, is GDPR compliant and all surveys were created on a KU Leuven licensed (protected) Qualtrics-account. As data of a personal and sensitive nature require to be transferred, stored, and handled with optimal guarantee for security and in accordance with EU privacy regulations, the data from the self-report questionnaires will be analyzed based on unique participant codes.

### 2.8 Statistical analysis plan

All analyses will be completed in accordance with CONSORT standards. Intent-to-treat analysis will be used. Our primary and secondary outcomes will be analyzed using analysis of variance (mixed ANOVA) with time (pre, post, 2-month follow-up) as a within-subjects factor, and condition (PET, CREAT) as a between-subjects factor. Any baseline differences will be covaried in analyses.

To take into account the repeated measure nature of the study, group differences for the continuous variables at post-training and at follow-up will be tested via a mixed ANOVA model. A model with a main effect for time and for group (PET program vs. CREAT program), random effects for the dummy variables representing time clustered within individuals, and an interaction between time and group will be run to detect changes between groups for the primary and secondary outcomes. Follow-up independent samples *t-*tests will be calculated to examine group differences at post-training and follow-up time points. To correct for the inflated risk of a Type I error from multiple comparisons, Benjamini and Hochberg's (65) false discovery rate procedure will be applied to the main outcomes (i.e., primary and secondary outcomes). Although sample size planning was based on mixed ANOVA modeling, multilevel analyses that take into account the dependence in the data at school-level (clusters) will also be conducted to account for possible variance due to school membership.

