## 2 Materials and methods

### 2.1 Study design and sample size

A cluster randomized controlled trial with a 2 (condition; PET program vs. CREAT program) × 3 (time point; baseline, post-training, and follow-up) factorial design was conducted. Classes of adolescents were asked to complete measures of the study outcomes at all three time points (see procedure).

A total sample of 130 adolescents (i.e., *N* = 65 for each condition) provides 80% statistical power to investigate the effectiveness of the PET program, with an alpha of 0.05 and estimated medium effect sizes of 0.25 (38). Given previous (large) effect sizes ranging from *d* = 0.82 (for increased specificity) to *d* = 1.78 (for anticipated pleasure) (11, 14), this more conservative effect size estimate will help mitigate against Type II errors. However, in anticipation of considerable drop-out rates, some oversampling was done. We intended to recruit 15% extra participants (based on drop out of ±17% in previous school study of our lab), resulting in an sample size of approximately 150 participants (75 per group).

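### The rule to covary whatever baseline differences appear lets chance imbalance choose the covariates; adjustment should be fixed in advance

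*Protocol article*

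**What the plan says.** The covariate rule in section 2.8 is one sentence: "Any baseline differences will be covaried in analyses". It names no variables, no criterion for a difference and no form of adjustment.

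The same section defines the analysis as a mixed ANOVA "with time (pre, post, 2-month follow-up) as a within-subjects factor, and condition (PET, CREAT) as a between-subjects factor". The fuller model statement has time, group "and an interaction between time and group will be run to detect changes between groups for the primary and secondary outcomes", and names no covariate. Group differences at the later assessments are then examined with independent-samples t-tests: "tests will be calculated to examine group differences at post-training and follow-up time points".

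Section 2.5.1 names one instrument for baseline control. The DASS-21 "was used to assess basic mental health to control for baseline differences in the training groups". It does not say whether this applies always or only when the groups differ, or whether the total or a subscale is meant.

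The candidates for a baseline difference are many. Section 2.5 lists five outcome constructs ("Primary outcomes are resilience and mental wellbeing. Secondary outcomes are positive affect, positive affect regulation and anhedonia"), and section 2.7 adds demographics ("Age and demographic data (month of birth, year of birth, gender, ethnicity, school, class, grade) were recorded").

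**The concern.** Under randomisation, baseline differences between arms are chance. A rule that adjusts only for differences that are seen has three effects:

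- The covariate set depends on the draw and can differ from one outcome to the next.
- A prognostic T1 score is left out when it looks balanced, although adjusting for it would still reduce residual variance.
- A gap just too small to be called a difference stays uncorrected.

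There is also a problem of form. The word 'any' does not exclude the outcome's own T1 score, and T1 is already one of the three repeated measures. If T1 is added as a covariate as well, the meaning of the time × group result depends on how it is entered, which the section does not say. The follow-up t-tests carry no covariate at all, so for them the rule cannot be followed.

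At stake are the power and the interpretability of the two primary comparisons.

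**Working it through.** **The plan's own figure.** Section 2.1 states that 130 pupils "provides 80% statistical power to investigate the effectiveness of the PET program, with an alpha of 0.05 and estimated medium effect sizes of 0.25". Reading 0.25 as Cohen's f gives d = 2 × 0.25 = 0.5. An exact two-sided two-sample t-test at 0.05 then needs 64 per arm (128 in total), and 65 per arm gives 80.8%. So 130 is reproduced as an unadjusted comparison at one time point. The point below does not turn on it.

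**Inputs.** From section 2.2: 95 pupils in PET and 93 in CREAT. Assumed, because the article gives none of them: a p < 0.05 screen for a difference, a pre–post correlation r of 0.5 to 0.7, a 0.3 SD effect, outcome SD 1 and no clustering.

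**1. How often chance triggers the rule.** With k independent variables the probability is 1 − 0.95^k: 23% for k = 5 (the outcome constructs), 26% for k = 6 (adding DASS-21) and 34% for k = 8.

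**2. Power.** The standard error of a post-score difference is √(1/95 + 1/93) = 0.1459. For a change score, multiply by √(2(1 − r)); for ANCOVA on T1, by √(1 − r²). Approximate power is Φ(0.3/SE − 1.96).

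| Analysis | r = 0.5 | r = 0.7 |
|---|---|---|
| Post score | SE 0.1459, 54% | SE 0.1459, 54% |
| Change (T2 − T1) | SE 0.1459, 54% | SE 0.1130, 76% |
| ANCOVA | SE 0.1263, 66% | SE 0.1042, 82% |

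The rule uses ANCOVA only in the few trials where T1 is flagged, so its power stays close to the unadjusted row. Simulation of the rule gives 53–56% if the post score is used otherwise and 54–75% if the change contrast is used otherwise, against 66–81% for ANCOVA in every case.

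**3. Type I error.** Overall, simulation gives about 3–5% under the rule, so there is no inflation. Conditional on a baseline gap b, with no treatment effect, the post-score difference is centred on r·b and the change difference on −(1 − r)·b, both with standard deviation 0.1459 × √(1 − r²). The screen misses any gap below 1.96 × 0.1459 = 0.286. Take b = 0.25:

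- Post score, r = 0.7: centre 0.175, SD 0.1042, rejection limit 0.286. (0.286 − 0.175)/0.1042 = 1.06, or about 14%.
- Post score, r = 0.5: centre 0.125, SD 0.1263. (0.286 − 0.125)/0.1263 = 1.27, or about 10%.
- Change, r = 0.7: centre −0.075, limit 1.96 × 0.1130 = 0.2215. (0.2215 − 0.075)/0.1042 = 1.41, or about 8% with both tails.
- Change, r = 0.5: the same as the post score, about 10%.

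Over all gaps above 0.2 SD that miss the screen, simulation gives about 10–14% (post score) and 6–12% (change), against 4–7% for ANCOVA.

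**4. T1 as both outcome and covariate.** If T1 enters with one coefficient c common to all times, the term c·T1 cancels from T2 − T1 and T3 − T1. With complete data the time × group contrast is then unchanged, and the imbalance is not adjusted there. If T1 enters with a separate coefficient at each time, each contrast becomes the ANCOVA contrast. In that model the T1 level itself has a group coefficient of exactly 0 and a T1 slope of exactly 1, so it carries no information.

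**The case against.** The strongest defence has four parts.

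**The detail may be elsewhere.** A condensed article may leave the covariate list to the full plan, and section 2.10 dates an OSF preregistration to September 2022, before the January 2023 baseline. This stands as a limit: a reader might infer that the adjustment set was still open once data were in hand, and the article does not show that. But the sentence printed is a rule, not an omission, and as a rule it is data-driven.

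**The stated model already uses baseline.** The time × group contrast works through change, so it keeps part of the gain from adjustment. This stands. A reader might infer that most of the benefit is lost. That fits the post-score t-tests, but not the main model, where the gap to ANCOVA is about 6–12 percentage points.

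**No error inflation.** A reader might infer that the nominal 5% fails. The simulations show no overall inflation from the rule; only the error conditional on an undetected gap is raised.

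**The plan does not say that T1 will be covaried, or that baseline tests will be run.** Also correct. DASS-21, the one instrument named for control, is neither a primary nor a secondary outcome. Double use of T1 is something the wording allows, not something announced. Nor do the documents support a claim that some covariate would be flagged in most trials. Figures such as 63% for six scales need pupil-level tests, a class ICC of 0.05 and independent scales, all assumed; related scales or a school share of the ICC lower them. However, section 2.5.1 neither makes DASS-21 adjustment unconditional nor limits 'any', so it does not repair the rule.

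**Conclusion.** The concern holds as a badly fixed covariate rule. Observed imbalance chooses the covariates, the set can vary by outcome, a prognostic T1 score is omitted when it looks balanced, and the way T1 would enter a model that already has it as an outcome is left open.

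The size is moderate. Against adjusting for T1 in every case, the rule loses roughly 6 to 12 points of power on the change contrast and more on the post-score t-tests. It also leaves conditional type I error up to about 14% when a sizeable gap goes undetected. Overall type I error is not affected.

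These figures rest on the assumed screen, effect size and correlations, and on no clustering. The direction does not depend on them: for any r between 0 and 1, 1 − r² is smaller than both 1 and 2(1 − r), so fixed adjustment is at least as precise in large samples.

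**What to change.** Replace the sentence with a covariate set fixed in advance and used whatever the observed balance: the T1 score of the outcome being analysed, school (pair) and, if wanted, T1 DASS-21, stating total or subscale.

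Choose one role for T1. Either analyse T2 and T3 with T1 as covariate, or keep T1 as an outcome with a common baseline mean in both arms, but not both. Take the T2 and T3 group contrasts from that model in place of the unadjusted t-tests. Put any adjustment for an unexpected imbalance in a labelled sensitivity analysis.

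The cost is a few lines of text, and all these variables are already collected. The downside is that covariates can no longer be added to the primary model after the data are seen. The change does not deal with dependence within classes: with an assumed class ICC of 0.05, pupil-level ANCOVA still had a type I error of 7–10%, so clustering needs its own handling.
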